#### Hypothesis tests

For each outcome model, an omnibus test of the Condition factor will test whether the outcome differs across study arms. Single-degree-of-freedom contrasts will test the specific hypotheses that PN+BUP is superior to PN, which in turn is superior to UC. The contrasts correspond to the Condition effect for endpoint analyses (e.g., treatment entry; early remission of DSM-5 OUD) or the Condition X Time interaction for repeated measures analysis of differential change (e.g., Quality of Life).

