**Results::**

The primary outcome is OUD treatment entry within 30 days of enrollment. Participants are assessed at baseline and followed at 3- and 6-months post-enrollment on measures of healthcare utilization, substance use, and general functioning. Challenges and recruitment adaptations pursuant to the COVID-19 pandemic are discussed.

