### Study Aims and Hypotheses

The trial will compare the study arms on three broad categories of outcomes.

*Aim 1* of the study is to determine the effectiveness of PN + BUP vs PN vs UC in facilitating OUD treatment entry (primary outcome) and retention in treatment.

*Aim 2* is to determine the effectiveness of PN + BUP vs PN vs UC in reducing opioid use, drug-related problems, and overdose events (fatal and non-fatal).

*Aim 3* of the study is to determine the effectiveness of PN + BUP vs PN vs UC in reducing incidence of HIV/STIs, increasing adherence to recommended sexual health care, and reducing HIV/STI related risk behaviors.

Our overarching hypothesis is that the PN + BUP arm will be superior to the PN only arm, which will be superior to UC. That is, we posit that PN + BUP will have superior OUD treatment entry compared to the PN and UC arms, and that entry and retention in OUD treatment will lead to reduced opioid use and related harms, improve HIV/STI treatment adherence, and reduce HIV/STI related behavioral risks.

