### Randomization, and Baseline Procedures

After the individual provides written informed consent, the RA administers the baseline assessments. Upon completion of all baseline assessments, the RA completes the randomization assignment and informs the participant of their study condition. Participants are assigned to conditions using a random permutation procedure and block sizes of 3, 6, and 9. RAs are blinded to randomization assignment during the administration of the baseline assessments. Participants receive compensation for the baseline assessment following randomization, in addition to receiving compensation ($40) for completion of each of the two follow-up assessments at 3- and 6-months.

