### Statistical Analysis

Outcomes will be examined via a generalized linear modeling framework (for endpoint analyses, such as OUD treatment entry), with extension to generalized linear mixed modeling for repeated measures models (for analyses of differential change, e.g., days of drug use).

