#### Explanatory variables

The explanatory variables in the statistical model will include: (1) *Study Condition* (*PN + BUP vs PN vs Usual Care)* and (2) *Recruitment Site (Clinic Site, Social Network, Other)*. For variables analyzed as repeated measures, the model will also include (3) *Time* and its interaction with *Condition*.

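### For repeated-measures outcomes the omnibus test is placed on Condition while the hypothesis contrasts are placed on Condition x Time, so the two test different effects in one model (minor)

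*Protocol article*

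**What the plan says.** All references are to the protocol article.

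- **Hypothesis tests**, opening sentence: "For each outcome model, an omnibus test of the Condition factor will test whether the outcome differs across study arms". The rule covers every outcome model.
- **Hypothesis tests**, closing sentence: the single-degree-of-freedom contrasts, which carry the specific hypotheses (PN + BUP over PN, PN over UC), correspond to the Condition effect for endpoint analyses "or the Condition X Time interaction for repeated measures analysis of differential change (e.g., Quality of Life").
- **Explanatory variables**: all models contain Condition and Recruitment Site. Repeated-measures models add Time and Condition x Time. No baseline covariate is listed.
- **Statistical Analysis**, opening sentence: endpoint outcomes use generalized linear models, "with extension to generalized linear mixed modeling for repeated measures models (for analyses of differential change, e.g., days of drug use").
- **Abstract (Results)**: "Participants are assessed at baseline and followed at 3- and 6-months post-enrollment on measures of healthcare utilization, substance use, and general functioning". Table 2 gives the same three time points for urine tests, ASI-Lite, quality of life and distress.
- **Randomization, and Baseline Procedures**: "Upon completion of all baseline assessments, the RA completes the randomization assignment and informs the participant of their study condition".

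**The concern.** Once a model contains Condition x Time, the Condition term no longer has one fixed meaning. What it estimates depends on how Time is coded and on whether baseline is among the responses. The section recognizes this for the contrasts, which it moves to the interaction, but leaves the omnibus test on Condition.

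Followed as written, the three-arm test reported for an outcome such as days of drug use or quality of life would concern a different quantity from the pairwise tests printed beside it. A non-significant omnibus result could stand next to significant contrasts. A significant one could reflect chance imbalance before randomization. Software coding defaults could decide which. The omnibus test is the only three-arm test the article names for these outcomes, which serve Aim 2: it "is to determine the effectiveness of PN + BUP vs PN vs UC in reducing opioid use, drug-related problems, and overdose events (fatal and non-fatal").

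**Working it through.** The article gives no effect size, alpha or power for these outcomes, so there is no stated figure to reproduce. The check has two parts.

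**1. What the Condition term estimates**

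Let D0, D3 and D6 be the arm differences at baseline, 3 and 6 months. Baseline precedes randomization, so the expected D0 is 0. Take baseline as a response visit.

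- *Time reference-coded at baseline:* Condition = D0. Its expectation is 0 whatever the treatment does, so the test rejects at rate alpha.
- *Sum-to-zero coding, three categorical visits:* Condition = (D0 + D3 + D6)/3. For an effect d sustained at both follow-ups this is (0 + d + d)/3 = 2d/3. For an effect growing linearly to d at 6 months it is (0 + d/2 + d)/3 = d/2.
- *Condition x Time:* the pair (D3 − D0, D6 − D0), which is differential change.

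**2. Illustrative size**

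From the article: three arms and an original target of 360. Assumed: equal arms of 120 (in line with permuted blocks of 3, 6 and 9), Gaussian outcome with SD 1 at each visit, compound symmetry with correlation ρ, complete data, two-sided alpha 0.05, and effects of 0, 0.2 and 0.4 SD for UC, PN and PN + BUP.

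The squared deviations of the arm effects from their mean of 0.2 sum to 0.04 + 0 + 0.04 = 0.08. Times 120, that is 9.6. The noncentrality parameter λ is 9.6 times the squared time profile divided by its variance.

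- *Baseline-coded Condition, 2 df:* λ = 0, so power = 5%.
- *Averaged Condition, 2 df:* the three-visit mean has variance (1 + 2ρ)/3.
  - Sustained: λ = 9.6 × (2/3)² × 3/(1 + 2ρ) = 12.8/(1 + 2ρ).
  - Linear: λ = 9.6 × (1/2)² × 3/(1 + 2ρ) = 7.2/(1 + 2ρ).
- *Joint Condition x Time, 4 df:* the two changes have covariance matrix (1 − ρ)[[2, 1], [1, 2]].
  - Sustained: λ = 9.6 × 2/(3(1 − ρ)) = 6.4/(1 − ρ).
  - Linear: λ = 9.6 × 1.5/(3(1 − ρ)) = 4.8/(1 − ρ).

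Power from the noncentral chi-square distribution (critical values 5.99 on 2 df, 9.49 on 4 df):

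| Effect | ρ | Baseline-coded Condition | Averaged Condition (λ) | Condition x Time (λ) |
|---|---|---|---|---|
| Sustained | 0.1 | 5% | 84% (10.67) | 55% (7.11) |
| Sustained | 0.3 | 5% | 72% (8.00) | 67% (9.14) |
| Sustained | 0.5 | 5% | 61% (6.40) | 83% (12.80) |
| Sustained | 0.7 | 5% | 53% (5.33) | 97% (21.33) |
| Linear | 0.1 | 5% | 58% (6.00) | 42% (5.33) |
| Linear | 0.5 | 5% | 38% (3.60) | 70% (9.60) |
| Linear | 0.7 | 5% | 32% (3.00) | 91% (16.00) |

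A simulation with generalized estimating equations (200 runs, ρ = 0.5, sustained effect) gave 5%, 56% and 86%. This agrees with 5%, 61% and 83% within simulation error: at 56% the standard error is √(0.56 × 0.44/200) = 3.5 percentage points.

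**The case against.** The strongest reply is that the section already shows its intent. It assigns the repeated-measures contrasts to Condition x Time, and the models are described as analyses of differential change. A sympathetic reader may take the omnibus test of Condition to mean the multi-degree-of-freedom arm comparison on whichever term suits the model. That is a fair reading of intent, but the sentence names a term and applies it to each outcome model, so it should be corrected rather than interpreted.

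Further points stand:

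- A reader might infer that the trial does not test the effects its aims ask about. The article does not support this: the specific hypotheses rest on the contrasts, these are on the right term, and nothing says that the omnibus test gates them.
- A reader might also infer that the omnibus test is null by construction. That needs baseline to be a response visit and the reference level of Time. The first is inferred from the wording on change and from the absence of a baseline covariate; the second is not stated. If only 3 and 6 months were responses, Condition would be a post-baseline difference.
- The averaged test does respond to treatment, and at low correlation it has more power than the 4-df interaction test.
- The power figures are illustrative. The article plans binomial and Poisson models, and its Sample Size and Power section leaves open a change of target or a collapsing of groups.

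Time coding and baseline handling may properly be left to a fuller document. Their absence is not the point; the point is the stated rule that conflicts with the rest of the section.

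**Conclusion.** The inconsistency is real and minor. For repeated-measures outcomes, the omnibus test and its contrasts are assigned to different terms of the same model. Given baseline as a response visit, the Condition term is not a test of differential change under either coding: it is uninformative about treatment under baseline reference coding, and under sum coding it carries two thirds of a sustained effect or half of a linearly growing one. The loss or gain in power relative to the interaction test depends on the assumed correlation, so the case for correction rests on testing the intended effect, not on a power advantage.

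Only the omnibus step for secondary repeated-measures outcomes is touched. The primary outcome, treatment entry within 30 days, is a binary endpoint without a Time term, so Condition is the correct term there. The same holds for other endpoint outcomes such as early remission. The single-degree-of-freedom contrasts are also unaffected.

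**What to change.** Replace the omnibus sentence with wording such as:

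> For endpoint models the omnibus test is the 2-df test of Condition. For repeated-measures models it is the joint test of all Condition x Time terms (4 df with three categorical visits, 2 df if time is linear). If baseline enters as a covariate or is constrained equal across arms, it is the joint test of the arm differences at follow-up.

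Add that the Condition main effect from a model with baseline as a response is not reported as a treatment test. The cost is one or two sentences, settled before analysis; no data collection, procedure or sample size changes.

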### Primary Outcome

The primary outcome is OUD treatment entry within 30-days post-enrollment, defined as admission to a buprenorphine provider (either office-based care or a specialty OUD program) or alternative OUD treatment modalities (e.g., methadone, medical detox followed by behavioral treatment). OUD treatment entry and retention will be collected by self-report. To the extent possible, treatment data will be verified via provider or treatment records with participants’ written permission. Treatment retention (defined as total number of days in MOUD treatment) will be examined as a secondary outcome. OUD treatment entry within 30-days of study enrollment is the primary outcome because linkage to such treatment is the main and most proximate goal of the service strategies being tested.

To assess for treatment entry and retention, at each follow-up assessment, participants are asked whether they enrolled in treatment for drugs or alcohol since their last assessment. If the participant reports one or more treatment episodes, research staff collect details of each episode including start/end dates, type of setting (e.g., inpatient, outpatient, detox), receipt of medication (e.g., buprenorphine, methadone), and whether they attended self-help groups.

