### Sample Size and Power

The study originally targeted recruitment of 360 participants. However, the COVID-19 pandemic led to significant challenges in recruitment. Efforts have increased substantially since the introduction of social network referrals; however, alternative design strategies may be considered because of low enrollment rates (e.g., adjustment to targeted sample size or collapsing groups).

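### The planned single-df contrasts leave out PN + BUP versus UC, a comparison that the primary-outcome hypothesis names

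*Protocol article*

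**What the plan says.** The Protocol article, Study Aims and Hypotheses, sets an ordering: "Our overarching hypothesis is that the PN + BUP arm will be superior to the PN only arm, which will be superior to UC". It then spells this out for treatment entry: "we posit that PN + BUP will have superior OUD treatment entry compared to the PN and UC arms". That names two comparisons for the combined arm, one against PN and one against UC.

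The Primary Outcome section fixes the endpoint: "The primary outcome is OUD treatment entry within 30-days post-enrollment".

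The Hypothesis tests section plans two layers. The first is general: "For each outcome model, an omnibus test of the Condition factor will test whether the outcome differs across study arms". The second is specific: "Single-degree-of-freedom contrasts will test the specific hypotheses that PN+BUP is superior to PN, which in turn is superior to UC". The contrasts listed are therefore PN + BUP versus PN, and PN versus UC. The article does not say whether the contrasts depend on the omnibus result, and it states no significance level or sidedness.

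On size, the Sample Size and Power section says: "The study originally targeted recruitment of 360 participants". It adds that the target may change.

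**The concern.** The hypothesis and the tests do not match. The comparison of the full package with usual care is hypothesized for the primary outcome but is absent from the contrasts that are meant to test the hypotheses.

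The planned tests do not replace it. A significant omnibus test says only that the arms differ somewhere; it gives neither a pair nor a direction. PN + BUP above UC could be inferred if both adjacent contrasts were significant. Under a strict ordering, though, those are the two smaller differences and their joint success is unlikely. A trial that followed the text exactly could show a clear PN + BUP versus UC difference and have no planned contrast with which to claim it. Adding the contrast after outcomes by arm are known would look post hoc.

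**Working it through.** **Inputs from the article.** Target 360 (Sample Size and Power). Three arms; equal allocation is inferred from block sizes 3, 6 and 9 (Randomization, and Baseline Procedures), so 360/3 = 120 per arm. Enrollment was 28 through April 2023 and 79 from May to July 2023, so 107 in all and about 36 per arm. The article gives no power figure to reproduce.

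**Assumptions.** Two-sided 5% tests. Entry rates are assumed and shown as a range. Eighty per arm (240 in total) illustrates a shortfall.

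**Power of single contrasts.** Normal approximation with pooled null variance: power = Φ{(|p1 − p2| − 1.96·√[2p̄(1 − p̄)/n]) / √[(p1(1 − p1) + p2(1 − p2))/n]}. At 120 per arm and 20/30/40%:

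- PN vs UC: (0.10 − 1.96 × 0.0559)/0.0555 = −0.172, giving 43%.
- PN + BUP vs PN: (0.10 − 1.96 × 0.0616)/0.0612 = −0.338, giving 37%.
- PN + BUP vs UC: (0.20 − 1.96 × 0.0592)/0.0577 = 1.456, giving 93%.

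The same formula at 80 per arm gives 31%, 26% and 79%. At 36 per arm and 20/35/50% it gives 29%, 25% and 77%.

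**Chaining against a direct test.** The two adjacent contrasts share the PN arm, so they are negatively correlated, and joint success is rarer than the product 0.43 × 0.37 = 16%. Binomial simulation at 120 per arm:

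| Assumed UC/PN/PN + BUP | Both adjacent contrasts significant | PN + BUP vs UC significant after a significant 5% omnibus test |
|---|---|---|
| 20/30/40% | about 9% | 87% |
| 10/20/30% | about 17% | 95% |
| 20/35/50% | about 43% | 99.6% |

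At 20/30/40%, in about 22% of trials neither adjacent contrast is significant but PN + BUP versus UC is, with no omnibus condition applied.

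**Familywise error when all arms are equal.** With equal arms the two listed contrasts have correlation −0.5.

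- Two contrasts, tested whatever the omnibus result: 1 − P(|Z1| < 1.96 and |Z2| < 1.96) = 9.1%.
- Two contrasts, only after a significant 5% omnibus test: 4.2% (simulation).
- Three contrasts, no omnibus condition: 12.2% (simulation).
- Three contrasts, only after a significant 5% omnibus test: 5.0% (simulation).

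The last result extends beyond the case of equal arms. With three arms, any two pairwise null hypotheses together imply that all arms are equal, so the omnibus test is the only intersection test needed. The procedure is therefore closed.

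**The case against.** The strongest reply is that little is lost. The model has a three-level Condition factor, so PN + BUP versus UC can be estimated directly from it. The omnibus test has roughly 87 to 88% power at 20/30/40% and 120 per arm, so a large difference would not go unnoticed, and success on both listed contrasts implies the missing one. All this is true, and it limits the point to one unnamed directional contrast. It does not remove the mismatch: being estimable is not being prespecified, and an omnibus result supports no claim about a pair.

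The power advantage also rests on the hypothesized ordering. If one step has no effect (20/20/40% or 20/40/40%), PN + BUP versus UC only ties the other non-null contrast, at 93% with 120 per arm.

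Two stronger readings are tempting, and the article supports neither.

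- A reader might infer that the contrasts are free 5% tests with familywise error near 9%. The text states no level or sidedness, and it places an omnibus test ahead of the contrasts without giving its role. Under two-sided 5% tests the error is about 4% or 9%, depending on that role; two one-sided 2.5% contrasts would give 5.0%. Such detail may sit in the full protocol or analysis plan, so its absence from the article is no finding.
- A reader might object to the contingency that "alternative design strategies may be considered because of low enrollment rates (e.g., adjustment to targeted sample size or collapsing groups", as data-driven pooling that must cost power. The stated trigger is enrollment, not outcomes, and no groups are named. Nor is pooling always weaker: at 120 per arm, pooling both navigation arms against UC gives 93.6% at 20/35/40% and 96.5% at 20/38/40%, against 92.7% for PN + BUP versus UC. Both rate sets keep the ordering.

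**Conclusion.** The point holds in a narrow form. For the primary outcome the article hypothesizes PN + BUP superior to UC but lists no contrast that tests it. Under the assumed strictly ordered rates at 120 per arm, chaining the two listed contrasts would establish it in only about 9% to 43% of trials, against 87% to 99.6% for the direct contrast tested after the omnibus test. The percentages rest on assumed entry rates, inferred equal allocation and two-sided 5% tests. The mismatch between the sections does not depend on them.

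Error control matters here because of the repair: a third contrast added with no rule would bring familywise error to about 12%, so the contrast and the role of the omnibus test should be settled together. This is a cheap improvement in wording; it does not show that the plan as written inflates error.

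**What to change.** In the Hypothesis tests section, for 30-day treatment entry:

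1. Add PN + BUP versus UC to the listed contrasts.
2. State that the 2-df omnibus test of Condition is done at 5%, and that the three pairwise contrasts are each tested at two-sided 5% only if it is significant.

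Make the change before outcomes by arm are seen. It needs no extra participants or data, and it keeps both contrasts already planned.

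The cost is that no contrast can be claimed when the omnibus test fails. For PN + BUP versus UC at 20/30/40%, power falls from 93% to 87% at 120 per arm and from 79% to 69% at 80 per arm. The lower figure in each pair is the one to quote for the repaired plan.

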### Sample Size and Power

The study originally targeted recruitment of 360 participants. However, the COVID-19 pandemic led to significant challenges in recruitment. Efforts have increased substantially since the introduction of social network referrals; however, alternative design strategies may be considered because of low enrollment rates (e.g., adjustment to targeted sample size or collapsing groups).

## PROGRESS TO DATE AND FUTURE DIRECTIONS

After a delayed start-up due to the COVID-19 pandemic and largely unsuccessful adaptations to recruit patients seen via telehealth, in-person recruitment at the two sexual health clinic sites commenced in November 2021. While research staff were able to successfully integrate into the clinic flow and screen a large number of patients for eligibility (>4000 patients), new challenges that continued to hinder study enrollment became apparent.

A significant challenge impacting recruitment has been the sustained reduction in patient volume, even as the clinics resumed in-person services following the COVID-19 pandemic. Services were limited to scheduled appointments only, which differs from the pre-pandemic model of high-volume, on-demand walk-in services. This has resulted in both fewer patients served at the sexual health clinics overall, and a different patient population than originally anticipated. Specifically, the rate of untreated OUD (the core inclusion criterion for the study) is lower than expected, based on preliminary data obtained in the feasibility pilot [11]. As of February 2023, walk-in services at the clinics have resumed, but rates of untreated OUD have remained low (see Table 3). Based on screening data for patients seeking sexual health services through July 2023 using the TAPS Tool and branching to questions about past 30-day opioid use, only 2.4% have endorsed any opioid use in the 30-days prior to screening. Eligibility rates were so low that the viability of the study was in question.

In response to low rates of eligibility and enrollment, we modified the protocol to expand recruitment beyond the sexual health clinic sites, while maintaining the originally planned screening activities at these sites. There has been some promise with in-person screening efforts because walk-in services have resumed, though not to the volume observed prior to the pandemic and corresponding shifts in clinical flow. As described above, recruitment procedures were adapted for recruitment using snowball sampling (i.e., social network member referrals from enrolled participants) and engagement with other healthcare and community sites to increase overall recruitment efforts.

The social network referral strategy has singularly improved recruitment efforts compared to the clinic screening. Between May 2023 and July 2023, 79 participants were enrolled—a significant increase in enrollment compared to those in 2021 and 2022. Using this novel recruitment strategy, we may be able to understand if Patient Navigation techniques can not only improve linkages to OUD treatment among sexual health patients, but also facilitate service linkage for those referred by their peers. Notably, this strategy has some parallels with how sexual health clinics already function in another domain, namely through disease intervention specialists that identify and treat partners of individuals with sexually transmitted infections. Evaluating these touchpoints as facilitators to OUD treatment may shed light on how researchers and clinicians can engage individuals with untreated OUD using novel strategies such as social network connection. These techniques may resolve barriers to engagement in research such as institutional distrust [43] by allowing potentially eligible participants to learn about research opportunities through their trusted peers. Furthermore, it is important to examine how social networks may be a viable pathway to encourage and empower individuals with untreated OUD to seek evidence-based treatment services that they otherwise would not pursue independently. Still, there are potential confounders that may be introduced through the use of social network referrals. Social support has been identified as a predictor of treatment entry and engagement, but findings are mixed [44-46]. It is possible that greater social network support may influence readiness for treatment entry. Thus, it will be important to consider the association of social networks, such as familial support, on the primary outcome of treatment entry in this study.

